#### Clinical evaluation workflow

2.6.2

ARF cases will be diagnosed if children meet 2015 modified Jones criteria (13) for high-risk populations. Nurses and physicians at participating facilities will confirm the diagnosis through laboratory tests, physical examination, and echocardiography. ARF diagnostic criteria included in SOPs and REDCap registry forms guide providers in confirming diagnostic criteria for enrollment.

Cases that are determined to be likely ARF are entered into the registry and their echocardiograms are uploaded for review by cardiologists. There are several participating cardiologists at tertiary care facilities in the capital city of Kathmandu who will provide diagnostic support and clinical advice as requested by study clinicians. Recruitment and follow-up will occur continuously, with structured follow-up visits scheduled at 3, 6, and 12 months post-enrollment for each ARF patient. Children requiring penicillin prophylaxis will be reviewed clinically in accordance with national follow-up guidelines. Follow-up will occur at the closest participating facility to the child's residence.

At each participating site, implementation is led by a designated clinical team comprising a physician, staff nurse, and laboratory technician. This team is responsible for application of ARF diagnostic criteria, echocardiographic assessment, registry documentation, and coordination of follow-up care.

Training was held by KIOCH in November 2025 during which SOPs for recruitment, ARF diagnostic criteria, and echocardiography protocols were reviewed with all providers and distributed. All facilities are expected to adhere to centrally defined SOPs and any deviations or contextual constraints will be documented in detail and reviewed during monthly monitoring and quality assurance meetings with the central KIOCH team.

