### Data collection and management

2.7

Clinical data from initial consultation will be collected using standardized electronic case report forms in REDCap, which comprises the registry. Echocardiographic images will be exported from the ultrasound machine to Tricefy, an online cloud-based repository, and linked by unique study IDs. Patients who have positive echocardiograms will be followed up at their local health facility monthly per clinic protocols, and at 3, 6, and 12 months they will be followed up per study protocols using a REDCap form. Echocardiographic quality will be monitored by cardiologists, and constructive feedback will be provided to performing physicians at the recruiting facilities as needed. Program delivery and data quality will be monitored through periodic review of REDCap registry completeness and monthly quality check-ins will be conducted by the central KIOCH team.

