### Outcome measures and data sources

2.8

Evaluation of the ARF case-finding program will use Proctor's taxonomy of implementation outcomes (8) with a primary focus on acceptability, feasibility, and adoption during early program delivery across diverse health system contexts in Nepal. Implementation outcomes are summarized in Table 1. Definitions and examples of Proctor's taxonomy outcomes are provided in Supplementary Table 1. These outcomes will be assessed primarily at the facility level to reflect integration of the standardized workflow into routine clinical practice. Implementation outcomes will be evaluated from April 2026 to April 2027, following a two-month run-in period.

**Table 1 T1:** Implementation outcomes evaluated in this study protocol, organized according to Proctor's taxonomy (8) with corresponding units of analysis, key evaluation questions, data elements, and data sources. The final row describes exploratory care-process indicators assessed at the patient and facility level during the first 12 months of program delivery; these are not Proctor outcomes and are not intended to evaluate clinical effectiveness. ARF, acute rheumatic fever; FCHV, Female Community Health Volunteer; QA, quality assurance; REDCap, Research Electronic Data Capture; SOP, standard operating procedure.

Proctor outcome(s)	Unit of analysis	Key questions addressed	Data elements	Data sources
Penetration	Facility/catchment	Are children with symptoms suggestive of ARF being identified and evaluated within routine care?	Number of children evaluated for ARF per site Number and characteristics of children enrolled with suspected or confirmed ARF Distribution by age, sex, distance to facility, and referral source	REDCap clinical data Facility clinical records
Acceptability	Provider/facility	Is the program acceptable to the people delivering it? Do providers and hospital administrators think it is adding to their workload.	Do providers agree with the program? Do providers think it is adding to the workload? Provider-reported perceived usefulness and acceptability	Provider/FCHV structured surveys Hospital superintendent structured surveys
Adoption	Facility/provider	Have participating facilities initiated and operationalized the standardized ARF case-finding and registry workflow?	Number and proportion of facilities initiating the full workflow Number and cadre of providers participating	Facility clinical records Provider structured surveys

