Feasibility	Facility/provider	Can the standardized workflow be delivered within routine inpatient and outpatient care?	Reported workflow barriers Time burden estimates Documentation of contextual constraints	Monthly monitoring reports Provider structured surveys
Fidelity	Facility/provider	Are ARF diagnostic and registry procedures implemented according to centrally defined SOPs?	Proportion of evaluations meeting Jones criteria documentation standards Echocardiography completeness and image adequacy Registry completeness Frequency and nature of protocol deviations	REDCap clinical data Monthly monitoring reports
Sustainability	Facility	Is the program still operational with sustained adherence at 12 months?	Continued ARF case enrollment activity Continued registry use Ongoing participation in QA processes Sustained workflow adherence	REDCap clinical data Monthly monitoring reports
—	Patient/Facility	How is the standardized workflow functioning clinically during early implementation?	Number and proportion of ARF diagnoses among evaluated children Diagnostic concordance with central cardiologist review Time from symptom onset to diagnosis Time from diagnosis to initiation of prophylaxis Follow-up completion at 3, 6, and 12 months	REDCap clinical data Facility clinical records

Exploratory care-process indicators will be assessed at the patient level and are intended to characterize whether the intervention may function to improve ARF care in the absence of pre-implementation comparator data. These include the number and proportion of ARF diagnoses among evaluated children, accuracy and timeliness of diagnosis, linkage to follow-up care, and follow-up completion over time. These measures are descriptive and are not intended to evaluate long-term clinical effectiveness.

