#### Data sources

2.9.1

Data sources include facility clinical records, REDCap clinical data, provider and hospital superintendent surveys, and monthly monitoring reports with site-based study leads.

Facility clinical records: We will examine the routine paper-based clinical forms that exist in the facilities. We will examine background data on participants, as well as monthly records for participants who are positive for ARF. At the end of the program, researchers will hand search clinical forms to extract relevant data.

REDCap clinical data: Three types of REDCap clinical data will be used for this study.
When a suspected case is referred to a participating facility, the study encounter and suspected diagnosis will be recorded in REDCap.If the case screens positive for ARF, their echocardiogram will be reviewed by a Kathmandu-based cardiologist who will report their echocardiographic findings in REDCap.Per study protocol, at three study points (3, 6, and 12 months) patients diagnosed with ARF will be monitored for progress. These visits will be conducted using REDCap forms.Provider surveys: Surveys will be distributed at 12 months to all providers (one doctor and one nurse at each facility). Surveys will consist of a mix of multiple choice, Likert-scale and free text questions. These will be conducted in a mix of English and Nepali and will be conducted through Google forms.

Hospital superintendent surveys: Surveys will be distributed at 12 months to the superintendent in charge of each facility enrolled in this study. Surveys will consist of a mix of multiple choice, Likert-scale and free text questions. These will be conducted in a mix of English and Nepali and will be conducted through Google forms.

Monthly monitoring reports: Once a month, a central researcher from KIOCH will hold a “monthly check-in” with each of the 11 site-based study leads. These free-form discussions will cover barriers and solutions encountered over the past month, as well as number of cases, perceptions of case mix, and any questions that have arisen. These check-ins will not have audio recording but the KIOCH researcher will take detailed notes.

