### Analysis

2.10

Analyses will be descriptive and exploratory, consistent with the pragmatic, non-randomized design and primary focus on implementation outcomes. Acceptability, adoption, feasibility, fidelity, penetration, and short-term sustainability will be summarized at the facility level using appropriate summary statistics. Results will be reported individually by facility and stratified by facility type (district vs. referral hospital) to characterize variation in implementation experience across site types.

Acceptability will be assessed through a simple summary statistics including means, and ranges of scores from providers surveys, and through a quantifying data found in provider and hospital superintendent surveys.

Adoption will be assessed through a narrative description of how workflows were deployed across facilities using data from provider surveys, REDCap clinical records, and facility clinical records.

Feasibility will be assessed quantitively through the percentage of workflows that are completed using data from REDCap clinical records and qualitatively through barriers reported in the provider structured surveys and monthly monitoring reports.

Fidelity will be quantified using adherence metrics including completeness of RedCap registry forms, echocardiographic protocol compliance, and documented protocol deviations from monthly monitoring reports.

Short-term sustainability will be evaluated quantitatively based on continued case enrollment, REDCap registry use, and participation in quality assurance processes at 12 months using data from REDCap activity logs and monthly reports.

Exploratory care-process indicators will be summarized at the patient level, including diagnostic patterns, concordance with central review, timeliness of diagnosis, and follow-up completion. In cases where initial diagnosis is unclear and reclassification occurs, final diagnoses will be used where possible. These measures are descriptive and not intended to assess clinical effectiveness. The study is not designed for formal between-facility comparisons. Patient-level registry data, provider-level survey data, and facility-level monitoring reports serve complementary descriptive roles and are not formally integrated through multilevel modeling, consistent with the pragmatic, single-arm design.

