### Ethical considerations

2.11

The study was approved on December 1, 2025, by the Nepal Health Research Council. Written informed consent will be obtained from parents or guardians, and assent from children aged 12 years or older for permission to participate in the PRIMA research study and for registry enrollment. Parents and children who do not wish to participate in the study will continue to receive routine care as medically indicated without inclusion in the registry.

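### Sections 2.6.2, 2.7 and 2.9.1 give inconsistent entry points for the REDCap registry, so workflow completion, Jones-documentation fidelity and ARF yield may be computed in a selected group of children

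*Protocol article*

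**What the plan says.** Three sections of the protocol article describe who gets into REDCap.

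- Section 2.6.2 (Clinical evaluation workflow): "Cases that are determined to be likely ARF are entered into the registry and their echocardiograms are uploaded for review by cardiologists". The same section says: "ARF diagnostic criteria included in SOPs and REDCap registry forms guide providers in confirming diagnostic criteria for enrollment". Both sentences put entry after at least part of the diagnostic work-up.
- Section 2.7 (Data collection and management): "Clinical data from initial consultation will be collected using standardized electronic case report forms in REDCap, which comprises the registry". This makes the REDCap forms and the registry the same thing, starting at the first consultation.
- Section 2.9.1 (Data sources): "When a suspected case is referred to a participating facility, the study encounter and suspected diagnosis will be recorded in REDCap". This is entry on suspicion, at referral.

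Three measures depend on who is recorded.

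- Section 2.10 gives feasibility, a primary outcome, one quantitative measure: "the percentage of workflows that are completed using data from REDCap clinical records".
- Table 1 lists under fidelity the share of evaluations whose Jones-criteria documentation meets the standard. Its sources are REDCap and the monthly monitoring reports.
- The exploratory row of Table 1 lists: "Number and proportion of ARF diagnoses among evaluated children".

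Table 1 also lists "Number of children evaluated for ARF per site" under penetration. Penetration and the exploratory row name facility clinical records as a second source. Section 2.11 says that families who decline "will continue to receive routine care as medically indicated without inclusion in the registry".

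**The concern.** Whether a child is in REDCap determines whether that child can be counted in any percentage drawn from REDCap. Under the Section 2.6.2 rule, a child who was assessed and ruled out leaves no row. Nor does a child whose echocardiogram or streptococcal test was never completed, so that no judgement of likely ARF was reached. These are the children in whom an incomplete workflow would show, and they belong in the denominator of a proportion among evaluated children.

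This matters more than a loose sentence usually would. Feasibility is a primary outcome, and this percentage is its only quantitative component. A statistical analysis plan can define a denominator, but it cannot recover children who were never recorded. Recruitment began in February 2026 and the evaluation window opens in April 2026. Results are to be shown by facility and by facility type, so sites that read the entry rule differently would produce percentages on different bases.

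**Working it through.** The protocol states no sample size, expected yield or completion rate, so there is no figure to reproduce. The main check is textual, followed by an illustration on assumed inputs.

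**Step 1. Are these two databases or one?** If Section 2.9.1 described an encounter form and Section 2.6.2 a later, separate registry, the rules would be compatible. Section 2.7 works against that reading, because it equates the REDCap forms, from the first consultation, with the registry. The entry points therefore concern the same database.

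**Step 2. Who is recorded under each rule?**

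| Child | Section 2.6.2 rule | Section 2.9.1 rule |
|---|---|---|
| Referred, judged likely ARF | recorded | recorded |
| Referred, ruled out | not recorded | recorded |
| Referred, work-up stalled | not recorded | recorded |
| Walk-in, ruled out | not recorded | unclear |

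The last row arises because Section 2.5 includes children who simply present at a facility, whereas Section 2.9.1 speaks of referred cases.

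**Step 3. Do the paper records fill the gap?** Section 2.9.1 describes that extraction as background data on participants and monthly records for ARF-positive participants. Participants may include children who are not ARF-positive, but the text does not clearly reach children who were never entered. Paper records are not named as a source for the workflow-completion percentage (Section 2.10) or for fidelity (Table 1).

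**Step 4. Effect on yield (assumed inputs).** Let s be the share of evaluated children judged likely ARF and c the share of those confirmed. Assume no child judged not likely is later confirmed.

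- All evaluated children recorded: yield = s × c.
- Likely cases only: yield = c.
- With s = 0.10 and c = 0.60: 0.10 × 0.60 = 6%, against 60%.
- With s = 0.50 and c = 0.80: 0.50 × 0.80 = 40%, against 80%.
- The ratio is 1/s: 10 at s = 0.10 and 2 at s = 0.50.

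**Step 5. Effect on workflow completion (assumed inputs).** Let a be completion in likely cases and b completion in the other evaluated children.

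- All evaluated children recorded: s × a + (1 − s) × b.
- Likely cases only: a.
- With a = 0.90, b = 0.50, s = 0.10: 0.09 + 0.45 = 54%, against 90%.
- With a = 0.90, b = 0.70, s = 0.50: 0.45 + 0.35 = 80%, against 90%.
- With b = a = 0.90: 90% under both rules, so no shift.

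**Step 6. Echocardiograms.** The same kind of conflict recurs. Section 2.6.2 has the echocardiograms of likely cases uploaded, Section 2.6.3 has all of them uploaded for central review, and Section 2.9.1 has central review if the case screens positive. Table 1 lists concordance with central review as an exploratory indicator. If only positives are reviewed, concordance cannot show cases missed locally.

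**The case against.** The best counter-argument is that Section 2.6.2 contains one loose sentence and the rest of the article points to broad entry. Section 2.6.2 does not say that only likely cases enter. Section 2.9.1, the section that defines the data sources, sets out a sensible sequence: encounter, central review if positive, then follow-up visits. Table 1 refers to children enrolled with suspected as well as confirmed ARF. Central SOPs, joint training and monthly review may already ensure uniform practice, and the study is descriptive, with no success thresholds and no formal comparison between facilities. Much of this stands. Broad entry may well be what is intended, and if it is followed the denominator largely exists for referred children. That is why the consequence is conditional. It does not remove the conflict, since Section 2.6.2 is the section that describes the clinical workflow and its wording ties enrollment to confirmed criteria. Descriptive percentages still need a known base.

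A reader might also infer more than the text supports:

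- *That yield would approach 100%.* Likely is not confirmed. Section 2.6.3 allows reclassification and Section 2.10 uses final diagnoses where possible.
- *That feasibility could not look poor.* Central review and the 3-, 6- and 12-month visits come after entry and can fail. Feasibility also draws on reported barriers from surveys and monthly reports.
- *That a site missing most symptomatic children would score the same as one missing none.* Penetration is a count, so it falls when children are missed.
- *That leaving out families who decline is an error.* It follows from requiring consent for the registry.

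Whether penetration should be divided by a catchment population is a separate question and not part of this point.

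**Conclusion.** The point holds as an inconsistency with a conditional consequence. The article gives one database inconsistent entry points. If sites follow Section 2.6.2, the workflow-completion percentage, Jones-documentation fidelity and the proportion of ARF among evaluated children are computed without those ruled out or stalled, and would probably be too favourable. The facility records as described do not clearly correct this.

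The size rests entirely on assumptions. Yield would be 6-40% among all evaluated children against 60-80% among likely cases, for 10-50% judged likely and 60-80% of those confirmed. Workflow completion would be 54-80% against 90%, if completion is 90% in likely cases and 50-70% in the others, and would not move if the two groups complete equally. The text does not show which rule sites are following, so it does not establish that bias has occurred.

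**What to change.** 1. Reconcile Sections 2.6.2, 2.7 and 2.9.1 into one entry point at initial evaluation. Open a minimal REDCap record for every consenting child evaluated for ARF, whether referred or walk-in, including those ruled out. It should hold the date, referral source, which Jones elements and echocardiography were done, and the outcome.
2. For families who decline, keep an aggregate count only, which is consistent with Section 2.11.
3. In Section 2.10 and Table 1, state evaluated children as the denominator for workflow completion, Jones-documentation fidelity and ARF yield.
4. Reconcile the echocardiogram upload and review statements in Sections 2.6.2, 2.6.3 and 2.9.1, and state which children form the denominator for concordance with central review.

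The cost is one short form, a tally for refusals and edits to the sections named. The downside is brief extra data entry for each child evaluated, and percentages that are likely to look less favourable. The change should be made early, because evaluations that go unrecorded may not be recoverable at the end of the programme.

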#### ARF diagnostic criteria

2.6.3

The 2015 modified Jones criteria (13) for high-risk populations will be used. The diagnosis of ARF is made if two major or one major and two minor criteria are met along with the evidence of streptococcal infection. If ARF is thought to be a recurrent episode, three minor criteria can be used to make the diagnosis. Major criteria include presence of carditis, mono- or polyarthritis, polyarthralgia, chorea, erythema marginatum, and subcutaneous nodules. Minor criteria include monoarthralgia, fever ≥38.0 °C, elevated inflammatory markers: ESR ≥30 mm/h and/or CRP ≥3.0 mg/dL, or prolonged PR interval on ECG. Prolonged PR interval is counted as a minor criterion only if carditis is not being used as a major criterion. There must be evidence of preceding group A streptococcal infection which is required for all except isolated chorea or indolent carditis. Antistreptolysin O Titer (ASOT) testing is provided to all facilities by the PRIMA study and will be the most common GAS antibody test used, though anti-DNase B titer, positive throat culture for GAS, and positive rapid antigen detection testing for GAS can also be used.

Carditis may be clinical or subclinical. Subclinical carditis is defined by Doppler echocardiographic evidence of pathological mitral or aortic regurgitation and morphologic changes as detailed in the 2023 World Heart Federation guidelines for the echocardiographic diagnosis of RHD (14). Echocardiographic assessments are performed using standardized imaging checklists which specifically include the criteria for pathological regurgitation and morphologic change. Echocardiograms are all uploaded for central review by cardiologists to support diagnostic consistency and fidelity. Kathmandu-based cardiologists serve as the final interpretive authority for echocardiographic findings, consistent with specialist referral practice within Nepal's health system. All clinics are equipped with a cardiac ultrasound machine.

Cases in which diagnostic criteria are not clearly met are reviewed by a study cardiologist, and children may be classified as suspected or probable ARF when appropriate. Diagnostic classification may be updated over time as additional clinical, laboratory, or echocardiographic information becomes available during follow-up, which reflects real-world practice.

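### Concordance with central cardiologist review can be inflated and partly circular unless it uses the site's diagnosis from before any cardiologist input

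*Protocol article*

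**What the plan says.** The protocol article gives the cardiologists several roles in the same diagnostic pathway.

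- **Adviser.** Section 2.6.2 describes several participating cardiologists at tertiary facilities in Kathmandu "who will provide diagnostic support and clinical advice as requested by study clinicians".
- **Reviewer of unclear cases.** Section 2.6.3: "Cases in which diagnostic criteria are not clearly met are reviewed by a study cardiologist". The child may then be classified as suspected or probable ARF, and the classification may change during follow-up.
- **Final echo authority.** Section 2.6.3: "Kathmandu-based cardiologists serve as the final interpretive authority for echocardiographic findings".
- **Central reader.** Section 2.9.1 says that for a case that screens positive, "their echocardiogram will be reviewed by a Kathmandu-based cardiologist who will report their echocardiographic findings in REDCap".

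Two measures depend on these readers. Table 1 (section 2.8) lists "Diagnostic concordance with central cardiologist review" among the exploratory care-process indicators, and "Echocardiography completeness and image adequacy" among the data elements for fidelity, a secondary outcome.

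Two statements bear on which site diagnosis is compared. Section 2.9.1 says that when a suspected case is referred, "the study encounter and suspected diagnosis will be recorded in REDCap". Section 2.10, in the paragraph on the exploratory indicators and directly after the sentence that names concordance, says: "In cases where initial diagnosis is unclear and reclassification occurs, final diagnoses will be used where possible".

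**The concern.** A concordance figure tells the reader how often the site would have reached the central reader's conclusion unaided. That needs two separate judgements. If a site asks a cardiologist, records what it was told, and a cardiologist from the same group then supplies the reference, agreement on that child says little about the site. The same applies to an unclear case that is reclassified after cardiologist review and then enters the comparison under its final label. These are the hardest cases, where concordance would be most informative.

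At stake is the meaning of one exploratory indicator. A figure raised by advice could be taken as evidence that district and referral teams classify ARF reliably by themselves, and it could be carried into scale-up plans on that basis. A smaller, related matter is image adequacy. Several cardiologists may judge it, fidelity is reported facility by facility, and the article does not mention recording which reader made each judgement.

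**Working it through.** The protocol states no sample size, expected concordance, advice rate or reader agreement, so there is no figure to reproduce. The check has a textual step and an illustration in which every input is assumed.

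**Step 1. Which diagnosis is compared?**

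- Section 2.9.1 records a suspected diagnosis at the encounter, so a site diagnosis from before central review may exist. The text does not say that it is entered before advice is sought, that it is kept unchanged, or that it is the one used for concordance.
- Section 2.10 points the other way for one subset: unclear cases that are reclassified are analysed under the final diagnosis where possible.
- By section 2.6.3, cases that do not clearly meet criteria go to a study cardiologist. In that subset a cardiologist has helped to set the label that is compared with cardiologist review. The overlap is partial, since a label may also change on later laboratory or clinical information.

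**Step 2. Size for concordance.** Let

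- c = agreement when the site decides unaided,
- f = share of cases with cardiologist input before the compared diagnosis is fixed,
- h = share of would-be disagreements that this input removes.

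Reported agreement = c + f × h × (1 − c).

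With f = 0.30:

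| c | h = 0 (site diagnosis fixed first) | h = 0.5 | h = 1 |
|---|---|---|---|
| 0.75 | 0.750 | 0.75 + 0.30 × 0.5 × 0.25 = 0.7875 | 0.75 + 0.30 × 1 × 0.25 = 0.825 |
| 0.80 | 0.800 | 0.80 + 0.30 × 0.5 × 0.20 = 0.83 | 0.80 + 0.30 × 1 × 0.20 = 0.86 |

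Reported agreement thus runs from about 79% to 86%, a rise of 3 to 7.5 points. Varying f with c = 0.80 and h = 1 gives 0.82 at f = 0.10 and 0.90 at f = 0.50.

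**Step 3. Size for image adequacy.** Suppose two readers would pass images of equal quality at 90% and 75%. The expected gap between two facilities is the difference in their reader mix times 15 points:

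- each facility read wholly by a different reader: 1.0 × 15 = 15 points;
- mixes of 80/20 and 20/80: 0.6 × 15 = 9 points;
- same mix: 0 points.

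For scale, at the average pass rate of 82.5% with 20 echocardiograms, one facility's sampling standard error is √(0.825 × 0.175 / 20) = 0.085, or about 8.5 points.

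**The case against.** The strongest reply is that much of this depends on what the article does not say. Read order, reader allotment and reader identity are matters for the SOPs and for the cardiologist over-read form listed in Table 2, and a condensed article may leave them there. The order of events in 2.6.2 and 2.9.1 (case recorded, then echocardiogram reviewed) is consistent with a site diagnosis that precedes review. Concordance is exploratory, image adequacy is one element of a secondary outcome, and section 2.10 disclaims formal comparisons between facilities. Cardiologist support is also part of the program, so agreement after advice could be a fair description of the workflow as a whole.

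Most of that stands, and it rules out three stronger readings that a reader might infer:

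- *That concordance is inflated as a matter of fact.* Inflation needs advice before the compared diagnosis is fixed, or use of the reclassified diagnosis. With h = 0 there is none.
- *That the adviser and the reader of a given child are the same person.* The text establishes only a common group of cardiologists.
- *That differences between facilities in echo adequacy reflect their readers.* Nothing says images are routed by facility. Central upload is equally compatible with a common reader mix, for which the expected effect is zero.

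The reply does not dispose of the final-diagnosis rule in 2.10. That is a stated analysis choice, placed beside the concordance measure, and it builds cardiologist input into the comparison for reclassified cases. A descriptive figure must still measure what its label says. If agreement after advice is what is wanted, the report should call it that.

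**Conclusion.** The point holds in conditional form. As written, the plan allows the concordance indicator to be raised, and made partly circular, for children on whom a cardiologist has already advised or whose diagnosis was reclassified after cardiologist review. A site diagnosis fixed before that input and used in the comparison would remove the problem.

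The illustrative rise of 3 to 7.5 points rests wholly on assumed values for unaided agreement, advice rate and effect of advice; the protocol supports none of them and none contradicts it. The reader effect on image adequacy is only a possibility to check, and at small facility numbers it may be hard to tell from sampling error. Acceptability, feasibility and adoption, the primary outcomes, are untouched. This is a worthwhile clarification of an exploratory indicator and not a flaw in the study's main aim.

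**What to change.** **Section 2.10.** State that concordance compares central review with the site's initial REDCap diagnosis, entered before any cardiologist input, and that the final-diagnosis rule does not apply to this indicator. Final diagnoses can still serve the other diagnostic summaries. Report concordance separately for cases with and without prior cardiologist advice. Tabulate image adequacy by reader as a descriptive check beside the facility results.

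**Section 2.7.** Add two REDCap fields: a yes/no item for cardiologist advice before the site diagnosis was entered, and a coded identity for the central reader. Fill them in as cases arise, since both may be hard to reconstruct after 12 months.

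**Cost.** Two extra fields per case, and smaller, less precise subgroups when concordance is split. No additional reads are needed, and neither the allocation of echocardiograms nor the giving of clinical advice has to change.
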